**DETAILED PROTOCOL:**

PRINCIPAL INVESTIGATOR: [name].

Co- Principal Investigator: [name].

TITLE OF STUDY: Structured therapy interruption in persons with acute HIV-1 infection

FUNDING: AIDS Research Center – NIH

1. BACKGROUND AND SIGNIFANCE:
2. Historical background:

In animal models of chronic viral infection, virus-specific helper cells are essential to maintenance of effective immunity. In the absence of CD4 cells, acute infection leads to transient CTL responses and lowering of viral load, but the CTL response subsequently wanes and virus replication increases (Matloubian, Concepcion et al. 1994; vonHerrath Yokoyama et al. 1996; Azjac, Blattman et al. 1998). In HIV-1 infection, the earliest and most glaring hole identified in the immune repertoire is the absence of virus-specific T helper cell (Th) responses (reviewed in Kalams and [name], 1998). Rarely have these responses been detected in person with chronic HIV-1 infection, and when they have been detected the levels have been low, with stimulation indices greater than 5 having rarely been reported (Berzofsky, Bensussan et al. 1988; Wahren, orfeldt-Mansson et al. 1989; Schwartz, Sharma et al. 1994; Pontesslli Carlesimo et al. 1995; Beretta, Weiss et al. 1996).

1. Preclinical and clinical studies:

Given the central importance of Th cells in antiviral immunity, we examined the HIV-1-specific T helper cell response in person infected with HIV for up to 19 years who have maintained stable CD4 cell counts and viral loads at the limits of detection by the most sensitive quantitative assays available, and compared these to persons with chronic progressive infection. In non-progressing persons, no or very weak virus-specific Th cell responses were detected, consistent with what has previously been reported in persons who fail to control HIV-1 viremia (Figure1A). In marked contrast, PBMC from non-progressors not only demonstrated virus-specific helper cell responses, but also these responses were of enormous magnitude (Figure 1B). Depletion studies revealed that the effector cells were CD4 positive, and examination of lymphokines triggered for release by these cells demonstrated the cells to be of the Th-1 type, in that IFN gamma but not IL-4 was produced ([name], Billingsley et al. 1997). Theses cells also secreted antiviral beta-chemokines in response to viral antigen (Cocchi, DeVico et Al. 1995), suggesting a mechanism whereby these cells might further contribute to containment of virus. These results have now been confirmed by a number of additional laboratories, as reported at the 6th Conference on Retroviruses and AIDS in Chicago in February, 1999.

The identification of potent virus-specific helper cell responses in persons who were successfully controlling viremia led us to address the question as to whether these cells were associated with control of viremia in a larger cohort. Ten persons who had never been treated with antiviral therapy were evaluated. In persons with high viral loads there was no evidence of virus-specific helper cell responses to either p4 or gp160, which is also what was observed in both high risk and low risk seronegative persons ([name], Billingsley et al. 1997). In contrast, in persons who were spontaneously controlling viremia in the absence of antiviral therapy, strong virus-specific helper cell responses were detected ([name], Billingsley et al. 1997). These same findings were confirmed in a second cohort of infected, untreated patients (unpublished data). These results provide the first evidence of a virus-specific immune response that is associated with control of HIV-1. Recently, the role of CTL in controlling HIV infection has been more firmly established as well. Transient depletion of CD8 cells results in a dramatic increase in viremia in SIV infected macaques (Schmitz, Kuroda et al. 1999; Xin, Bauer et al. 1999). Other studies in humans have shown that adaptively transferred CTL localize at sites of infected cells in vivo (Brodie, Lewinsohn et al. 1999). At least one cross sectional study in humans indicates that there is a negative correlation between CTL and viral load (Ogg, Jin et al. 1998).

Based on our findings of strong Th cell responses in persons who are controlling viremia, and on the detection of strong cytotoxic T lymphocyte (CTL) responses in these persons (Harrer, Harrer et al. 1996), we hypothesize that cellular immunity might be critical to immune regulation in this infection. In response to infection, Th cells are activated to provide help in orchestrating an effective immune response, as one would expect in any viral infection, that is mediated at least in part through CTL. However, because HIV-1 is able to selectively infect activated CD4 cells, we hypothesize that these cells should immediately become infected and deleted. This in turn would lead to insufficient Th cells to maintain CTL responses, and thus CTL responses induced during acute infection would progressively diminish. The progressive loss of CTL is in fact what is observed in the majority of infected persons (Klei8n, van Baalen et al. 1995), consistent with this hypothesis.

These results provide firm evidence that HIV-1 can induce a strong CD4-positive T helper cell response directed against the relatively conserved p24 core protein. In some persons strong responses to the envelope protein gp160 are also generated. Precisely how some individuals are able to generate these responses and become long-term non-progressors is not clear, but may have to do with the relative magnitude of the initial viremia experienced in primary infection. The finding that these responses can be detected in all persons if treated with potent antiviral therapy during acute HIV-1 infection indicates that the induction of these responses is the rule, but that these responses are lost in the early stages of infection in the vast majority of infected persons. The p24-specific proliferative responses correlate with control of viremia ([name], Billingsley et al. 1997), providing the first evidence that HIV-1 specific immunity is involved in controlling the viral set point. The mechanism of viral inhibition by these cells is likely mediated through CTL, which are able to lyse infected cells before progeny virions are produced (Yang, Kalams et al. 1996). In the acutely treated patients, we have now detected strong HIV-1 specific T helper cell responses in 12 of 12 tested, which are analogous in breadth, magnitude and specificity to those seen in long-term non-progressors.

The ability to control viremia after stopping therapy may not be the case for all persons treated in acute infection, as suggested by a recent report of a person who was treated during acute HV-1 infection and stopped therapy 6 months later, at which time he experienced a recurrence of symptomatic acute HIV-1 infection (Daar, Gai et al. 1998). However, this person had no detectable CTL responses at the time that therapy was stopped, and t helper cell responses were not measured. Thus far all persons that we have treated in the acute stages of infection have maintained viral loads below the limits of detection, and have progressively generated strong CD4 T helper cell responses and the majority (5 of 6 tested thus far) have also generated detectable CTL responses. We propose now to test whether these responses are sufficient to control viremia by interrupting therapy in persons who have developed this immunologic phenotype.

Alternatively, we propose to test whether transient exposure to autologous virus will boost the breadth or magnitude of immunity to HIV-1 such that enhanced immunologic control can be achieved.

Conducting this study has important potential benefits to both the patient and to society. For the individual patient, therapy may be able to be discontinued, diminishing the physical and psychological consequences of the strict multi-drug regimens, and potentially limiting the development of side effects that are becoming increasingly apparent with long-term use of these drugs (Miller, Daly et al. 1998). If viral load is not contained, then allowing a brief period of viral replication may lead to augmentation of existing immune responses when antiviral therapy is re-instituted, such that effective immunity may ultimately be achieved. The benefit to society of these studies is that we may be able to determine the correlates of protective immunity, which would have profound implications for vaccine development and for therapeutic interventions. An additional benefit is that we may be able to determine whether “immunization” with autologous virus is able to boost endogenous immune responses.

1. SPECIFIC AIMS:

We hypothesize that early intervention with potent antiretroviral therapy confers immunologic maturation, which allows for immune control of HIV-1 replication without the need for ongoing drug therapy. Alternatively, we hypothesize that if breakthrough of virus replication is observed, this will provide a boost in HIV-1 specific immunity after reinstitution of antiviral therapy. Primary endpoints will be: (1) time to viral rebound to 200,000 copies/ml and (2) incidence of viral rebound to 200,000 copies/ml. Secondary objectives will be to correlate immunologic and virologic parameters with this beneficial effect including (1) effect on HIV-specific T helper cell responses, (2) effect on HIV-specific CTL responses, and (3) effect on virus genotype. Specifically, we propose to:

1. Discontinue anti-HIV-1 drug therapy in persons treated during the acute infection, who meet the following criteria:
2. Antiviral therapy for at least 4 months, with HIV-1 load of less than <400 RNA copies/ml for at least 2 months, and less than 50 RNA copies/ml prior to stopping therapy.
3. Detectable CD4 T helper cell responses to HIV-1 p24 (delta cpm greater than 500).
4. At least one assay for HIV-1 specific CTL. CTL responses may be detectable or non-detectable.
5. Monitor HIV-1 specific viral load after discontinuation of therapy using an ultra-sensitive RNA quantitation assay (lower limit of detection 50 RNA copies/ml).
6. Reinstitute antiviral therapy when the viral load reaches >200,000 RNA copies/ml, or when it is above 5,000 copies for Re-stop therapy after viral load is suppressed to <50 copies/ml for at least 8 weeks. Parameters for re-starting therapy will be used as above. Each subject will have therapy stopped a maximum of four times.
7. Virus will be genotyped each time it returns to ensure that resistance is not developing. If resistance does develop, then the patient will be informed and an alternative regimen suggested to which the virus is predicted to be sensitive, based on genotype. In persons who develop drug resistance, no further discontinuation of therapy will be pursued.
8. Summary of parameters to be monitored:
9. Time to recurrence of viral load> 200,000 copies
10. Incidence of recurrence of viral load > 200,000 copies
11. Effect on CTL
12. Effect on T helper cell responses
13. Effect on virus genotype
14. Effect on CD4 count
15. SUBJECT SELECTION:
16. Inclusion criteria:

1. CD4 proliferative responses in fresh PBMC of greater than 500 cpm to HIV-1 p24, using the standard assay ([name], Billingsley et al. 1997).

2. Antiviral drug therapy, three drugs, instituted during seroconversion, as defined by an indeterminate Western blot, or detuned ELISA or the clinical picture3.An HIV-1 load for at 2 months of <400 RNA copies/ml.

1. An HIV-1 load at the time of entry into the study of less than 50 RNA copies/ml (i.e., below the limits of detection by the ultra-sensitive assay).
2. Ability to give informed consent.
3. CD4 cell count within the normal range as per MGH hematology laboratory parameters.
4. Minimum Hgb of 11 gm/dl
5. Exclusion criteria:
6. Persons who do not meet the inclusion criteria.
7. Pregnant women or women intending to get pregnant during the time of the trial.
8. Age less than 18 years.
9. HIV-1 related opportunistic infections.
10. Other illness that would interfere with interpretation of the data, such as immunologic disorders or disorders requiring the use of immunomodulatory agents.
11. Vaccinations within 4 weeks prior to study entry.
12. Restarting therapy including Abacavir due to risk of hypersensitivity reaction.
13. Evidence of HIV drug resistance, as shown by the presence of major, well known drug mutations.

Source of subjects: Subjects will be recruited from an existing cohort of persons with documented acute HIV-1 infection who were treated with potent antiviral therapy. Persons have been followed at MGH in the Outpatient ID Clinic, referred by their primary care physician, or other outpatient clinics of the MGH, or other health care facilities.

1. SUBJECT ENROLLEMENT:
2. Methods of enrollment: Persons will be enrolled from an existing cohort of persons who have been treated with acute HIV-1 infection.
3. Procedures for obtaining informed consent: Informed consent will be obtained by the PI or Co-PI. Consent will be obtained prior to stopping therapy after extensive discussion.
4. Treatment assignment/randomization: N/A.
5. STUDY PROCEDURES:
6. Study visits and parameters to be measured: After the initial screening and enrollment visits, persons will be seen at least for the first 24 weeks, and then monthly. With a total of 30 visits for the first year. In Year 2, visits continue monthly, for a total of at least 12 visits. The following parameters will be measured:
7. Time to viral rebound: Virus load by ultra-sensitive PCR assay (Roche) will be determined at each of the follow-up times, with results available within 48-72 hours. Time to viral rebound and the rate of rise of viremia will be measured. Additionally, patients may be immediately evaluated by a study physician for any inter-current illness. This requires 1 ml of plasma.
8. CD4 proliferative responses: CD4 proliferative responses to p24 and gp160 will be performed each week for the first 8 weeks, and then every two weeks. This requires 15 ml of blood.
9. CTL precursor frequency assays (CTLp): CTLp will be measured every other week, to Gag, Pol, Env and Nef, using standard cytotoxicity assays. This requires <5 ml of blood.
10. CD4 cell counts; CD4 cell counts will be obtained once a week for the first four weeks, then every other week for the next 20 weeks, and then monthly. This requires 3 ml of blood.
11. If persons present with a febrile illness, the investigators may choose to perform the following additional tests or refer the person to the PCP:

# Influenza Titer

Mono spot

Strep test

Serologies for other common viral illness

This will help assess if the febrile illness is related to the study or not.

Estimation of blood volume required for these assays: 25 ml of blood will be required pre-enrollment for baseline assays. For the first 8 weeks, up to 75 cc’s of blood will be drawn weekly. For the next 16 weeks, 60 cc’s of blood will be drawn per week. A total of 600 cc’s will be taken for the first 8 weeks, 960 cc over the next 16 weeks, and up to 360 cc over the next 6 months. In years two through seven, up to 960 cc’s of blood will be drawn over the course of the year.

Contact with study subjects: Drs. [name], [name], [name], or the study nurse will speak with each subject by phone frequently during the duration of the trial. [name] will be available by beeper 24 hours a day. Subjects and their health care providers will have ongoing real-time access to the clinically relevant parameters and will discuss patient management issues with the PI on a regular basis.

1. Drugs to be used; N/A.
2. Devices to be used; N/A.
3. Procedures/surgical interventions: N/A.
4. Data to be collected and when data are to be collected: The data to be collected are outlined in section A above. The data will be collected at each visit.
5. Reinstitution of therapy: Therapy will be re-instituted for any single viral load of greater than 200,000 RNA copies per ml of plasma. If a plateau of viremia of greater than 5,000 RNA copies per ml of plasma is achieved, then antiviral therapy will be reinstituted. The same antiviral therapy that had been taken at the time of enrollment into this study will be re-instituted, excluding Abacavir which can not be restarted. unless there is evidence of resistance by genotyping. Therapy will be re-instituted for any sustained CD4 cell count decrease of 25% from baseline. Persons will subsequently be monitored on a weekly basis with viral load, CD4 T helper cell responses, and CTL assays to determine whether viremia is suppressed and whether an augmentation of HIV-1 specific immunity is observed. Persons will subsequently be monitored on a weekly basis with viral load, CD4 T helper cell responses, and CTL assays to determine whether viremia is suppressed and whether an augmentation of HIV-1 specific immunity is observed. CD4 cell counts are measured every other week.

After restarting therapy, the visit schedule is weekly until the HIV RNA is <50 copies per ml plasma. The viral load <50 must be sustained for at least an eight week period, when persons will once again be given the opportunity to stop therapy. At this point, if persons elect not to stop therapy, the visit schedule changes to onece a month, and the option of stopping therapy remains open if the viral load continues to be <50 copies/ml.

1. Re-stopping of therapy: In persons who experience a rebound in Viral Load after stopping therapy, drugs will be restarted as above (F) and subjects will be monitored. After 8 weeks of undetectable vial load (<50 RNA molecules per ml) they will be given the option of stopping therapy a second time under the same conditions of evaluation as occurred after the first interruption in therapy. Therapy will be re-instituted using the same criteria as in (F) above. Patients will be treated for at least 8 weeks with viral load less than 50 copies when they will once again be given the option to stop therapy, as in (F) above. The cycle can continue for a maximum of four interruptions.
2. Early study termination: This study will be discontinued in individuals noted to develop significant antiviral genotype resistance. Any subject with evidence of new mutations in bulk PCR product, not present in pre-treatment baseline plasma RNA (suggesting evolution of antiretroviral resistance) will result in termination of study and no further attempts to discontinue therapy will be done.
3. If a person chooses to go against the protocol criteria and guidelines to stop or start therapy on their own, they may continue on an observational follow up status. Their care would be directed by their Primary Care Physician and not the study guidelines.

As a suggestion of the IRB comments on 5/6/03: Clarification of follow up to read:

Long term follow up of these patients consists of clinic visits every 6 weeks, in which safety parameters, i.e., CD4 and viral load are performed in addition to experimental immunologic assays.

1. BIOSTATISTICAL ANALYSIS:
2. Specific data variables being collected for the study:
3. Viral load
4. T helper cell responses
5. CTL precursor frequency
6. CD4 cell counts
7. Times to viral rebound and rate of viral rebound
8. Viral genotype for resistance mutations

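### The stated yearly blood maximum does not hold for participants who stop therapy again: at the protocol's own weekly volumes a 24-week repeat stop takes up to 1,560 cc, against 960 cc a year

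*Protocol*

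**What the plan says.** All references are to the protocol, section Study Procedures, unless stated.

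- **Blood volume estimate.** "For the first 8 weeks, up to 75" cc are drawn each week. "For the next 16 weeks, 60" cc are drawn each week. The totals are 600 cc for the first period, then "960 cc over the next 16 weeks, and up to 360 cc over the next 6 months". After that: "In years two through seven, up to 960" cc in a year. These are years in the study.
- **Visits.** There are 30 visits in the first year, which fits 24 weekly and 6 monthly visits. Year 2 is monthly, with at least 12 visits. A later clarification puts long-term follow-up at every 6 weeks.
- **Reinstitution of therapy.** After a restart: "Persons will subsequently be monitored on a weekly basis with viral load, CD4 T helper cell responses, and CTL assays". Visits stay weekly until HIV RNA is below 50 copies/ml, and that level must then hold for at least eight weeks before another stop is offered.
- **Re-stopping of therapy.** The second stop takes place "under the same conditions of evaluation as occurred after the first interruption in therapy", and the cycle may run to four interruptions.
- **Listed assays.** Each assay has its own volume and interval (used in the check below).
- **Biostatistical Analysis, Statistical methods.** Time to rebound and rate of rise are to be compared across successive stops.

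**The concern.** The estimate follows one course only: a single stop, 24 weeks of weekly visits, then monthly visits. The annual figure for years two to seven equals 12 x 80 cc, which suits monthly visits and leaves no room for a new weekly phase. But restarting and re-stopping are part of the design, and a longer time to rebound at later stops is one of the results the study looks for. A long repeat stop is therefore a hoped-for outcome, and it is the case in which the stated maximum fails most clearly. The maximum is a figure about participant burden and safety, so it should be true for the participants who cycle.

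**Working it through.** **1. The plan's own totals reproduce.** 8 x 75 = 600 cc. 16 x 60 = 960 cc. Year 1: 600 + 960 + 360 = 1,920 cc (1,945 with the 25 ml baseline draw).

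**2. A 24-week repeat stop in years two to seven, at the first-stop weekly volumes.**

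- Total: 600 + 960 = 1,560 cc, which is 1,560 / 960 = 1.63 times the annual maximum, or 600 cc over.
- Week at which 960 cc is reached: 8 + (960 - 600)/60 = 14. At week 15 the total is 1,020 cc.
- Weeks 9-24 alone use the full 960 cc.
- If the 24 weeks fall evenly across two study years, the parts are 840 and 720 cc, and neither part alone exceeds 960 cc.

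**3. A repeat stop in the second half of year 1.** Its first 8 weeks take up to 600 cc, against 360 cc stated for those six months.

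**4. A repeat stop ended by rebound.** Off-therapy draw: 4 x 75 = 300 cc at 4 weeks; 8 x 75 = 600 cc at 8 weeks; 600 + 4 x 60 = 840 cc at 12 weeks. None passes 960 cc by itself, so the weekly post-restart visits decide. The protocol gives no volume for them.

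Assumptions for a range:

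- Post-restart draws cover the listed assays only: T helper 15 + CTL 5 + CD4 3/2 (every other week) + viral load 2 (1 ml plasma taken as 2 ml blood) = 23.5 cc.
- Re-suppression takes 4, 8 or 16 weeks, and weekly visits continue through the 8-week hold, giving 12, 16 or 24 weekly draws.
- There is one repeat stop, starting with the study year; the remaining weeks have one 23.5 cc visit every 4 weeks.

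Year total = off-therapy draw + 23.5 x weekly draws + 23.5 x (remaining weeks / 4):

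| Rebound at | 12 weekly draws | 16 weekly draws | 24 weekly draws |
|---|---|---|---|
| 4 weeks | 300 + 282 + 211.5 = 793.5 | 300 + 376 + 188 = 864 | 300 + 564 + 141 = 1,005 |
| 8 weeks | 600 + 282 + 188 = 1,070 | 600 + 376 + 164.5 = 1,140.5 | 600 + 564 + 117.5 = 1,281.5 |
| 12 weeks | 840 + 282 + 164.5 = 1,286.5 | 840 + 376 + 141 = 1,357 | 840 + 564 + 94 = 1,498 |

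Seven of nine courses exceed 960 cc. If visits in the 8-week hold were every 4 weeks instead of weekly, each total falls by 6 x 23.5 = 141 cc, and five of nine exceed it. If the participant stops again as soon as allowed, with weekly visits through the hold, the totals over the same nine courses run from about 1,634 to 2,544 cc.

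**5. What the listed assays need in a 24-week stop.** T helper (8 + 8) x 15 = 240; CTL 12 x 5 = 60; CD4 (4 + 10) x 3 = 42; viral load 24 x 1 ml plasma = 24. The sum is 366 cc. Taking 1 ml plasma as 2.5 ml blood (an assumption), viral load becomes 60 and the sum 402 cc.

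**The case against.** The case for leaving the text alone has four parts.

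- **The figures are an estimate with ceilings.** Weeks 1-8 are given as up to 75 cc, so 1,560 cc is an upper figure. This stands. But weeks 9-24 carry no such qualifier and fill the annual maximum alone.
- **The same evaluation need not mean the same volume.** This also stands: the re-stopping text fixes the evaluation, not the cc. Still, the only volumes the protocol attaches to that evaluation are the 75 and 60 cc.
- **Participants who rebound early do not breach by the stop alone.** Correct, as step 4 shows. Any excess then rests on draws that the protocol does not cost.
- **The 960 cc may hold some reserve for repeat stops.** What it covers is not stated. It exceeds the late year-1 rate (2 x 360 = 720 cc a year) by 240 cc, which pays for only 240 / 75 = 3.2 weekly draws at the start of a stop.

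A reader might also infer more than the text supports. One inference is that later stops must be sampled less, so that the across-stop comparison is biased or the plan cannot be followed. Step 5 speaks against it: the listed assays of a 24-week stop fit well within 960 cc at unchanged intervals, and viral load, on which time to rebound rests, needs 1 ml plasma per visit. The visit schedule (monthly in Year 2, six-weekly in long-term follow-up) bears more directly on that comparison than blood volume does. Another inference is that a cycling participant always exceeds the year-1 total, reaching 3,240-3,480 cc. That range assumes 60 cc at each post-restart visit, which the protocol does not state. With the listed assays only, the range is about 1,630-2,540 cc, which lies on both sides of 1,920 cc.

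**Conclusion.** The point holds as an inconsistency between the blood estimate and the re-stopping and restart rules. A repeat stop with more than 14 weeks of draws at the first-stop volumes inside one of years two to seven exceeds the stated maximum, by up to 600 cc at 24 weeks. For shorter stops the result depends on unstated post-restart draws; under the assumptions in step 4, many but not all courses exceed 960 cc. The stated sums are themselves correct; what fails is their coverage of participants who stop again. No bias in the endpoint follows from this. The consent pages are not at hand, so whether they give a volume per stop cannot be checked.

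**What to change.** Rewrite the estimate by phase instead of by study year:

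- one volume for each off-therapy period and one for each weekly post-restart period;
- totals for participants with two, three and four stops;
- a statement of which visit schedule applies to a repeat stop in Year 2 or later.

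Then reconcile the per-visit draw, the listed assay volumes, the visit schedule and the annual maximum, so that the maximum is true for participants who cycle, and match the consent wording.

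The cost is about a paragraph of protocol text and the matching consent text. Either the stated total becomes less favourable, or the per-visit draw is brought closer to the listed assay volumes. The second route is ample for one 24-week repeat stop (about 370-400 cc), but it should be summed before it is relied on for a participant who cycles all year: 52 weekly draws of 23.5 cc would be 1,222 cc. No clinical limit on blood volume is proposed here.

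### Stops 2 to 4 are offered on viral load without checking that CD4 has recovered, and the restart rule leaves 'baseline' and 'sustained' undefined

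*Protocol*

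**What the plan says.** **When therapy may be stopped again.** In the Protocol, Study Procedures, the paragraph on the period after restarting requires that suppression below 50 copies/ml "must be sustained for at least an eight week period, when persons will once again be given the opportunity to stop therapy". For a participant who declines at that point, "the option of stopping therapy remains open if the viral load continues to be <50 copies/ml". The item on re-stopping repeats the 8-week rule and offers "stopping therapy a second time under the same conditions of evaluation as occurred after the first interruption in therapy". Specific Aims gives the same condition. The only other limits are the bar on further stops once resistance appears and the maximum of four interruptions.

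**When therapy must be restarted.** Besides the viral load triggers, the item on reinstitution of therapy says: "Therapy will be re-instituted for any sustained CD4 cell count decrease of 25% from baseline". The item on re-stopping carries this into later cycles: "Therapy will be re-instituted using the same criteria as in (F) above".

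**What is measured.** After restart, "CD4 cell counts are measured every other week". Off therapy, the schedule is weekly for four weeks and then every other week for 20 weeks.

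**What is foreseen.** The sixth risk under Risks and Discomforts is a CD4 fall that is not reversed by renewed treatment.

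**The concern.** The stop rule and the restart rule look at different things. The stop rule looks only at viral load, while the restart rule also looks at CD4. A participant can be fully suppressed for 8 weeks and still have a CD4 count a quarter below where it began. This is the outcome the protocol lists as a risk, and nothing in the re-stop rule screens for it.

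Two undefined words decide what follows. *Baseline* is not tied to a cycle, and *sustained* is not given a number of counts. Depending on how they are read, the participant is at the restart threshold on the day of the stop, or the threshold has moved down with the participant's own incomplete recovery. What is at stake is renewed viremia in someone with reduced CD4, and the use of one of at most four stops on an interruption that may end almost at once.

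**Working it through.** The protocol gives no figure to reproduce here (its power analysis is marked as not applicable). The check compares the rules and then works out the size under stated assumptions.

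**1. Conditions side by side.**

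| Decision | Viral load | CD4 | Other |
|---|---|---|---|
| First stop (inclusion criteria) | <400 for 2 months, <50 at entry | Within the laboratory's normal range | T helper response, no resistance |
| Stops 2 to 4, including a deferred stop | <50 for at least 8 weeks, continuing <50 if deferred | None | No resistance; four stops at most |
| Restart, all cycles | >200,000 once, or plateau >5,000 | Sustained 25% fall from baseline | – |

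The paragraph on the period after restarting does not limit the reason for restart, so it covers a restart for CD4 loss as well as for viremia.

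**2. Two readings of baseline.** The blood-volume estimate places baseline assays before enrolment: "25 ml of blood will be required pre-enrollment for baseline assays". No re-measurement of baseline before later stops is described.
- *Fixed baseline.* The restart line is 0.75 × baseline. For assumed baselines of 500, 800 and 1,200 it is 375, 600 and 900. A suppressed participant at or below the line satisfies the stop rule and is at the restart threshold.
- *Baseline reset each cycle.* A participant who recovers only to 75% gets a new floor of 0.75 × 0.75 = 56% of the entry count.

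**3. Time off therapy under a fixed baseline.** This depends on what *sustained* means.
- On-therapy counts qualify: restart is due on the day of the stop, 0 weeks.
- Two off-therapy counts needed: about week 2 on the weekly schedule.
- Four needed: about week 4.

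The next offer then needs at least 8 more suppressed weeks.

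**4. Counts already in hand.** 8 weeks ÷ one count per 2 weeks = about 4, if every-other-week counting continues through the suppressed period.

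**5. Chance holds under a CD4 check.** Take a fully recovered participant, with independent lognormal variation of CV c on the baseline count and on each later count. The log-scale SD is s = √ln(1 + c²), and z = ln 0.75 / (√2 · s). Two later counts compared with one baseline share its error, so their correlation is s²/(2s²) = 0.5.
- One-count rule: Φ(z).
- Two-count rule: Φ₂(z, z; 0.5), the bivariate normal probability.

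| Assumed CV | s | z | One count low | Two counts both low | Second low, given first low |
|---|---|---|---|---|---|
| 10% | 0.0998 | −2.04 | 2.1% | 0.4% | 17% |
| 15% | 0.1492 | −1.36 | 8.6% | 2.6% | 30% |
| 20% | 0.1980 | −1.03 | 15.2% | 5.9% | 39% |

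The last column is the two-count value divided by the one-count value. It is well above the one-count value because a baseline that happened to be high affects every later comparison. A chance hold can therefore outlast one repeat count. The CVs are assumptions; the protocol gives none.

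**The case against.** **The conflict depends on an undefined word.** A reader might infer that the protocol plainly offers a stop to someone who already meets its own restart rule. The text does not go that far. It holds only if baseline is fixed before the first interruption and on-therapy counts can make a fall sustained. The evidence for a fixed baseline is indirect: a blood-volume line, and a sentence in Risks and Discomforts about the latently infected cell pool, not CD4. This objection stands and limits the claim. It does not remove the gap, because the per-cycle reading lowers the floor.

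**In one branch there is no exposure.** If on-therapy counts qualify, the restart rule cancels the stop on the same day. This is correct. The 2- and 4-week figures arise only if off-therapy counts are needed.

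**The re-stopping item covers only viral rebound.** Its opening does speak of persons with a rebound. The preceding paragraph has no such limit, and a viral-load restart can itself come with a CD4 fall.

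**The same conditions apply to later stops.** A reader might take "stopping therapy a second time under the same conditions of evaluation as occurred after the first interruption in therapy" to import the entry criteria. The phrase refers to evaluation after the first interruption, that is, to follow-up. Even if the normal-range criterion carried over, a count can fall 25% and stay in range whenever the upper limit is at least 4/3 of the lower.

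**Safeguards exist.** Stopping is optional, the restart rule stays in force, and "Subjects and their health care providers will have ongoing real-time access to the clinically relevant parameters". These are substantial and keep the severity low. They rely on judgement or act after the stop; none is a written bar to the offer.

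**Conclusion.** The point holds in a limited form. No re-stop condition asks for CD4 recovery, although CD4 loss compels restart and non-recovery is a named risk. On a fixed baseline, a participant at or below 75% can be offered a stop at the restart threshold, with 0 to about 4 avoidable weeks off therapy depending on how *sustained* is read. On a resetting baseline, the floor falls.

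The documents do not support calling this an outright contradiction or an unprotected safety failure, since both key words are undefined and several safeguards apply. They also give no data on how many participants would be affected. The schema to which the study endpoints item refers is not shown and could not be checked. Severity: worth considering.

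**What to change.** Add three statements to the items on reinstitution and re-stopping:
1. Baseline in the 25% rule is, for all cycles, the CD4 count before the first interruption, preferably the mean of the available pre-interruption counts.
2. Sustained means two consecutive counts.
3. No re-stop is offered, including a deferred one, while the two most recent on-therapy counts are both at or below 75% of baseline.

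The third statement uses the same test as the restart rule, so stop and restart can no longer disagree. Averaging the baseline reduces the error shared by all later comparisons.

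**Cost.** A few sentences of wording. No extra visit or blood is needed: counts are taken every other week after restart, and monthly once a stop is deferred. Later cycles will be somewhat fewer and more selected, which should be kept in mind when time to rebound is compared across stops. With a single-count baseline, about 0.4%, 2.6% or 5.9% of fully recovered participants would be held by chance at assumed CVs of 10%, 15% or 20%. Because the baseline error is shared, such a hold may last more than one count.
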